### Statistical methods

Statistical analysis will be based on an intention-to-treat (ITT) basis, comparing outcomes from all nurses allocated to the two trial arms. Findings will be reported according to the CONSORT guidelines for parallel-group randomized trials [47].

Personal socio-demographic information and job-related characteristics will be summarized descriptively according to the treatment arms. Categorical data will be presented as frequencies and percentages. Means, standard deviations, medians, interquartile ranges, and minima and maxima will be presented for continuous data. To verify the success of randomization, the baseline characteristics of the two treatment groups will be compared: continuous variables will be compared with a *t*-test (for normally distributed variables) or the Mann-Whitney *U* test (for non-normally distributed variables). Categorical variables will be evaluated with the chi-square or 2-tailed Fisher exact test. Change scores will be calculated. Data will be presented as percentages for categorical data and means and standard deviations for continuous data; 95% CIs will be used to indicate uncertainty around the estimates.

Follow-up data will be analysed using mixed models to establish the correlation between repeated measurements and examine main effects and their interaction, adjusting for the baseline score. The presence of multi-collinearity, interaction, and higher power terms will be assessed to check final model validity. Statistical significance will be defined at two-sided *p* < .05. All analyses will be carried out using Stata 17.0 for Windows.

The effects of baseline covariates expected to have an important influence on the primary outcome will be controlled for by comparing covariate-adjusted analyses with unadjusted analyses. Certain covariates that will be considered at baseline will refer to demographic variables (e.g. gender, age, and education level), the organizational context, and participation in non-mindfulness support courses.

The ITT principle will allow for potential biases arising from loss to follow-up, under the assumption that missing outcomes are missing at random (MAR) using Little and Rubin’s terminology (2002) [48]. Mixed models will allow for the inclusion of data from nurses with incomplete observations at follow-up. We will allow for the presence of missing outcome data on the assumption that the data are missing completely at random, conditional on the covariates included in the models (i.e. missing at random), again using Little and Rubins’ terminology [48]. Multiple imputation methods will be applied in the event of missing data.

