### Assignment of interventions: allocation

Participants will be randomly allocated to the intervention or the WL control group with an allocation ratio of 1:1. Participants allocated to the experimental group will receive the intervention immediately after randomization, and those assigned to the control group will be offered the same intervention 6 months after. The experimental intervention will take place over 6-weeks. The pre-test, post-test, and 1-month follow-up will be carried out at the same time for both study groups.

The trial statistician will prepare the sequence of treatments randomly permuted into blocks of 2. The randomization schedule will be generated with Stata software (version 17.0; Stata Corp, Corp, College Station, TX, USA) using the ‘ralloc’ command for random allocation of treatments balanced in blocks. The Emotional Exhaustion sub-scale (EX) score of the MBI-GS assessed at the screening phase will be used to perform a stratified randomization based on the median value (EX ≥ median vs. EX< median). Two lists of randomizations will be generated according to the levels of the stratification variable. The trial statistician will communicate by email the randomization results to the responsible for trial, who will notify to the participants by email if they belong to the intervention or the WL control group.

The trial will begin in September 2022. Enrolment will end as soon as the expected number is reached (36 for the intervention group and 36 for the control group). Before the intervention, participants randomly assigned to the intervention group will be divided into three subgroups consisting of 12 individuals. Each subgroup will follow the mindfulness courses (led by the same instructor) for 6 weeks. The courses will be delivered every Monday for subgroup 1, Tuesday for subgroup 2, and Wednesday for subgroup 3. Nurses will attend the intervention during working hours as part of the continuing professional education (CPE) courses provided by the Verona Hospital Trust Administration.

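### Randomisation is stratified on screening emotional exhaustion, but the analysis names neither the stratum nor the screening score and leaves 'unadjusted' undefined; the effect on the planned mixed model is small

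*Protocol article*

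**What the plan says.** Under 'Assignment of interventions: allocation', the EX score from the screening phase "will be used to perform a stratified randomization based on the median value". The article adds that "Two lists of randomizations will be generated according to the levels of the stratification variable", with the "sequence of treatments randomly permuted into blocks of 2" and a 1:1 ratio.

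Under 'Statistical methods', follow-up data go into mixed models that "examine main effects and their interaction, adjusting for the baseline score". Influential baseline covariates are then to be "controlled for by comparing covariate-adjusted analyses with unadjusted analyses". The covariates named are demographic variables, the organisational context and participation in non-mindfulness support courses. Neither the stratum nor screening EX appears, and unadjusted is not defined.

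Table 2 puts eligibility screening at −T1, allocation at T0 and the pre-treatment assessment at T1. The text below it identifies baseline with T1. The baseline score in the model is therefore a different measurement from the one that defines the strata. Under 'Outcomes', the primary outcome is change in EX from pre-treatment to 1 month after treatment.

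**The concern.** Stratified blocks force the arms to be nearly balanced on a variable that probably predicts the outcome. The treatment difference then varies less from trial to trial than under simple randomisation. An analysis with no term that carries this information reports a standard error that is too large. Its type I error falls below 5% and power is lost.

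Two things are at stake: whether the planned mixed model has this fault, and whether the unadjusted analysis has it. If the unadjusted analysis does, a difference between adjusted and unadjusted results would partly reflect a misstated standard error and not the covariates.

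**Working it through.** **The plan's own figure.** Inputs from 'Sample size': difference 1.21, SD 1.8, two-sided 0.05, 36 per arm. The standard error of a plain two-group comparison is 1.8 × √(2/36) = 0.424. Exact noncentral-t power is 79.2% at 35 per arm and 80.3% at 36, so 72 in total reproduces.

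**Treatment-only comparison of follow-up EX.** A median split of a normal variable retains 2/π = 0.637 of the variance that the variable explains. With r the screening–follow-up correlation (assumed), the true standard error is about 0.424 × √(1 − 0.637r²):

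- r = 0.4: 0.424 × √0.898 = 0.40
- r = 0.5: 0.424 × √0.841 = 0.39
- r = 0.6: 0.424 × √0.771 = 0.37

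The analysis would still report about 0.424.

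**T1-adjusted model.** What the stratum can add is limited by the partial correlation of screening EX (s) with follow-up EX (y) given T1 EX (b): (r_sy − r_sb·r_by) / √[(1 − r_sb²)(1 − r_by²)]. For r_sb = 0.7, r_by = 0.5, r_sy = 0.5 this is 0.15 / √(0.51 × 0.75) = 0.24. Even continuous screening EX then removes only 0.24² ≈ 6% of residual variance, or about 3% of the standard error.

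**Simulation.** 10,000 trials per row, 72 participants, median split on screening EX, permuted blocks of 2 within stratum, SD 1.8, true difference 0 or 1.21. Linear models at one follow-up time stand in for the mixed model. Cells show type I error / power in %.

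| r_sb, r_by, r_sy | Treatment only | + stratum | + T1 EX | + T1 EX + stratum | Change score, no covariates |
|---|---|---|---|---|---|
| 0.85, 0.5, 0.45 | 3.6 / 82.0 | 5.1 / 85.4 | 4.9 / 89.8 | 5.0 / 89.4 | 3.8 / 81.0 |
| 0.85, 0.7, 0.65 | 2.3 / 83.8 | 5.0 / 90.5 | 5.2 / 97.2 | 5.2 / 97.3 | 5.0 / 95.5 |
| 0.7, 0.5, 0.5 | 3.4 / 82.4 | 5.0 / 86.7 | 4.8 / 89.8 | 5.1 / 90.3 | 5.0 / 80.2 |
| 0.95, 0.6, 0.58 | 2.9 / 82.7 | 5.2 / 88.7 | 5.1 / 94.1 | 5.0 / 93.9 | 3.8 / 89.6 |
| 0.4, 0.6, 0.3 | 4.5 / 80.7 | 5.2 / 82.2 | 5.2 / 93.6 | 5.2 / 93.5 | 4.7 / 88.5 |

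Monte Carlo error on a 5% rate is √(0.05 × 0.95 / 10,000) = 0.2 points.

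- Treatment only: reported over true standard error runs from 0.425/0.417 = 1.02 to 0.425/0.366 = 1.16.
- T1-adjusted: the two agree within about 1% (for example 0.369 and 0.369; 0.304 and 0.306). The stratum moves power by at most about 0.5 points.
- Last row: it resembles a secondary outcome, whose baseline score is on another scale and only weakly related to screening EX. The baseline-adjusted model is still at 5.2%.

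A second simulation, also on assumed correlations, gives 4.4–5.1% for the T1-adjusted model, with its standard error within about 3% of the true one. Adding the stratum changes power by under 1 point; adding continuous screening EX changes it by about 0 to 1.6 points. The treatment-only comparison there has type I error 2.5–4.2%, with the standard error overstated by about 3–14%. Its power is about 81–83%, against 83–89% with the stratum.

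**The case against.** A reader might infer that the planned models' standard errors do not match the randomisation. The documents do not support that. The model adjusts for the baseline score, which for the primary outcome is EX on the same scale that defines the strata. T1 is indeed a separate measurement from screening, but this makes almost no difference to the results above. This objection stands in full.

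Unadjusted need not mean treatment only. The word comes after baseline adjustment has been fixed and is set against demographics, organisational context and support courses. It may mean the baseline-adjusted model without those extras, and then no analysis is left exposed. The primary outcome is also a change, and the article says change scores will be calculated. A covariate-free change-score comparison had type I error of 3.8–5.0% in the table. This objection also stands, but it depends on a reading that the article leaves open.

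The covariate list is loosely worded, and a full analysis plan may name the stratum. So the omission alone is weak. The point rests on an article that sets out its analysis variables, omits the one its design supplies, and commits to an undefined comparison.

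A reader might also infer that T1 EX is reported after participants know their arm. Table 2 orders allocation before T1, but nothing states when the allocation email arrives relative to the T1 questionnaire.

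**Conclusion.** The point holds as a modest clarification. The T1-adjusted mixed model is close to valid without the stratum, and its standard errors are not materially wrong. Conservatism appears mainly if unadjusted means a treatment-only comparison of follow-up EX: type I error about 2.5–4.2% in one simulation and 2.3–4.5% in the other. Even then there is no excess of false positives, and power stays above the planned 80%.

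All sizes rest on assumed correlations, approximate normality and a single-time-point simplification of the mixed model. The entry threshold of EX at or above 2.20 narrows the range of screening scores and may push the correlations, and so the conservatism, towards the lower end.

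**What to change.** Add to 'Statistical methods' that the randomisation stratum, or preferably continuous screening EX, is a fixed covariate in the primary and all secondary models. Define the unadjusted analysis as the one adjusted for the stratification factor only, so that the comparison with the covariate-adjusted analysis isolates the additional covariates.

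The cost is a sentence or two and one degree of freedom. Screening EX is already collected for everyone randomised. One practical step follows from 'Data collection and management': the password that links a nurse's questionnaires is generated at the baseline evaluation, so the screening score and stratum should be carried deliberately into the analysis file with the allocation. The expected gain in the T1-adjusted model is small, about 0 to 1.6 power points. The clearer benefit is an unadjusted result whose standard error fits the design.

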### Oversight and monitoring

As has been noted, participants who experience (serious) adverse events and harm resulting from the intervention or those allocated in the waiting list who experience a worsening of their mental health status will be referred to the Psychiatric Consultation Service at the Psychosomatics Unit and the project management group; they, however, will be excluded from the study. The ethics committees will be also informed.

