### Outcomes

As the proposed intervention aims to mitigate the prolonged strain on hospital staff by working with the most severe or critical COVID-19 patients, burnout—a specific indicator of chronic work-related dysfunctional response—was selected as the main outcome of interest. In particular, any change in the sub-subscale of emotional exhaustion (EX) between pre-treatment and 1-month post-treatment was chosen as the primary outcome of burnout [37]. Emotional exhaustion is a psychological construct that explores the perception of physical and emotional fatigue. It is characterized specifically by a lack of energy required to handle daily life and the prevalence of feelings of apathy and emotional detachment at work. It is the central dimension in burnout [38] and correlates strongly with job performance, absenteeism, higher psychopathological risk, and poor organizational effectiveness [39]. Numerous studies have found EX in HCWs to be associated with acute depressive symptoms, anxiety disorders, sleep problems, and poor quality relationships with patients [1, 33–35].

The secondary outcomes of the intervention will be to observe any change between pre-treatment and post-treatment and between pre-treatment and 1-month post-treatment, in:Professional efficacy (MBI-GS) [37]Cynicism (MBI-GS) [37]Depressive symptoms (PHQ-9) [40]Anxiety symptoms (GAD-7) [41]Post-traumatic symptoms (IES-R) [42]Insomnia (ISI) [43]Perception of stress (PSS) [44]Mindfulness skills (FFMQ) [45]Evaluation of self-criticism and self-reassurance (FSCRS) [46]

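### Nurses who are harmed, or who worsen on the waiting list, are to be excluded after randomisation, which contradicts the intention-to-treat analysis and makes missing at random doubtful

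*Protocol article*

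**What the plan says.** Oversight and monitoring names two groups: "participants who experience (serious) adverse events and harm resulting from the intervention", and "those allocated in the waiting list who experience a worsening of their mental health status". Both are to be referred to the psychiatric consultation service and the project management group, and the ethics committees are to be informed. The sentence then adds that "they, however, will be excluded from the study". No instrument, threshold or time point defines worsening.

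Statistical methods says: "Statistical analysis will be based on an intention-to-treat (ITT) basis, comparing outcomes from all nurses allocated to the two trial arms". The Sample size section also puts the calculation on an intention-to-treat basis. For missing outcomes, Statistical methods assumes missing at random given the model covariates, and states that "Mixed models will allow for the inclusion of data from nurses with incomplete observations at follow-up". Multiple imputation is to be used if data are missing.

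Under Outcomes, the change in emotional exhaustion "between pre-treatment and 1-month post-treatment was chosen as the primary outcome of burnout".

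The Oversight sentence presents itself as repeating something already stated. The earlier text, under Interventions, provides only for recording adverse events in either group, reporting serious ones and referring nurses who need support. It mentions no exclusion. Nowhere does the article say that an excluded nurse completes T2 and T3, or that her data are kept.

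**The concern.** An exclusion after randomisation that is triggered by how the participant fares breaks the comparison that randomisation set up. Here the trigger is close to what the trial measures. Depression, anxiety, insomnia, stress and post-traumatic symptoms are secondary outcomes, and the Outcomes section itself links emotional exhaustion to depression, anxiety and sleep problems.

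The trigger is also worded differently by arm: harm from the intervention on one side, worsening mental health on the other. Losing waiting-list nurses who worsen flatters the control arm and hides benefit. Losing intervention nurses who were harmed flatters the programme and hides harm. Which effect dominates depends on how many nurses each arm loses, and that cannot be known in advance.

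The missing-data plan is affected too. A nurse excluded before T2 has no post-baseline value at all. One excluded between T2 and T3 lacks the 1-month outcome. In either case the reason may be a deterioration that no scheduled questionnaire recorded.

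**Working it through.** **1. The texts side by side.** Statistical methods requires outcomes from every allocated nurse. Oversight and monitoring removes some allocated nurses from the study. For such a nurse both instructions cannot be carried out in full, and no other text resolves this.

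**2. The plan's own figure.** Inputs from Sample size: 36 per arm, difference -1.21, SD 1.8, two-sided 0.05, equal-variance t-test.
- Noncentrality = 1.21 / (1.8 × √(2/36)) = 2.85 on 70 degrees of freedom.
- Power = 80.3%; with 35 per arm it is 79.2%.

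The stated 80% with 36 per arm reproduces, so the sample size arithmetic is not at fault.

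**3. Worst-case illustration.** Assumptions, none of them in the document: normal scores; a fraction p of one arm is excluded; the excluded are exactly those with the worst exhaustion scores; all their data are dropped; two-sample t-test.
- Mean shift = 1.8 × φ(z)/(1−p), with z the (1−p) normal quantile.
- Remaining SD = 1.8 × √(1 − zλ − λ²), with λ = φ(z)/(1−p).
- p = 0.10: λ = 0.1755/0.90 = 0.195; shift 0.351; SD 1.52; 32.4 nurses left.
- p = 0.20: λ = 0.2800/0.80 = 0.350; shift 0.630; SD 1.37; 28.8 nurses left.

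| Excluded | True difference | Apparent difference | Chance of p < 0.05 |
|---|---|---|---|
| none | -1.21 | -1.21 | 80% |
| worst 10% of waiting list | -1.21 | -1.21 + 0.35 = -0.86 | about 55% |
| worst 20% of waiting list | -1.21 | -1.21 + 0.63 = -0.58 | about 29% |
| worst 10% of intervention arm | 0 | -0.35 | about 13% |
| worst 20% of intervention arm | 0 | -0.63 | 31 to 33% |

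Ten per cent of an arm is 3.6 nurses, so a handful of exclusions is enough.

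**4. Exclusions in both arms.** Under the same model, equal fractions leave the mean difference unbiased. Dropping the worst 4 of 36 in each arm still raises the type I error to 8.4%, because truncation shrinks the observed variance. If one common threshold applied to both arms (a change above +1.8), it would remove 4.7% of the intervention arm and 15.9% of the waiting list, and -1.21 would become -0.88.

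**5. With a likelihood model that uses T2.** Assumptions: T2 data kept, T2–T3 correlation 0.6, true difference -1.21, exclusions after T2 from the waiting list only.

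| What drives exclusion | 10% excluded | 20% excluded |
|---|---|---|
| the score seen at T2 | about -1.20 | about -1.20 |
| a trigger correlated 0.5 with T3 exhaustion | about -1.09 | about -1.03 |
| T3 exhaustion itself | about -0.96 | about -0.78 |

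The planned type of analysis therefore removes the bias, halves it or leaves much of it, depending on whether observed data carry the reason for exclusion.

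**The case against.** The sentence stands in a section on oversight and protection, not in the definition of the analysis set. It may mean only that the nurse stops participating and that data already collected are kept. Statistical methods would then govern, with mixed models that accept incomplete follow-up. This reading is possible and makes the problem smaller. It does not remove it: her later questionnaires, including the 1-month primary outcome, would still be missing because she fared badly, and the article does not state this reading.

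The step 3 figures are also harsher than the trial is likely to be. The trigger is adverse events or mental health status, not the exhaustion score. The rule reaches both arms, and adverse events can be recorded in either. The planned analysis is not a t-test on completers. A 20% harm rate in the intervention arm has no basis in the document, whose Discussion reports no evidence of side effects. All of this stands, so those figures are an upper end and not a forecast.

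A reader might infer that the missing data are not at random by design and that no mixed model or imputation can repair them. The document does not support that. If the worsening is visible at baseline or T2, missing at random can hold and the model copes, as step 5 shows. A reader might also infer that safety follow-up stops for these nurses. The text says the opposite about care: they are referred and the ethics committees are informed. At most, the trial questionnaires stop.

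**Conclusion.** The contradiction is on the face of the protocol and should be resolved before any nurse is excluded under it. An exclusion that depends on how a nurse fares cannot stand beside an analysis of all allocated nurses. It also leaves the missing-at-random assumption resting on whether observed data happen to capture the worsening.

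The size is unknown, because the document gives neither an exclusion rate nor a link between the trigger and exhaustion. The direction is unknown as well. At the upper end, one-sided removal of 10% to 20% of an arm could cost about 0.35 to 0.63 points of a planned 1.21, or create a spurious benefit of that size. With T2 data kept and worsening visible there, the bias could be close to nil. Claims that the bias is irreparable, or that these nurses are left without care, go beyond the text.

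**What to change.** Reconcile the adverse-event text under Interventions, the Statistical methods and the Oversight and monitoring section. Replace the exclusion clause with a data-retention rule along these lines: 
- Referral, or leaving the programme or the waiting list, does not remove a nurse from follow-up or from the analysis.
- She is analysed in the arm to which she was randomised.
- She is asked to complete T2 and T3 unless she withdraws consent to data collection.
- Referrals and adverse events are reported by arm.

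This concerns data only. Whether and when a nurse is referred or stops the programme remains for the investigators to decide.

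The cost is one sentence in the protocol and a matching line in the consent material. The sample size does not change: with all outcomes retained, the stated 72 nurses and 80% power stand.

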### Dissemination of findings

The results will be presented in international peer-reviewed journals if accepted. The principal investigators, co-investigators, and other professionals involved in the proposed intervention will be the authors of any publications. The criteria established by the International Committee of Medical Journal Editors will be adopted. Entitlement to authorship will be based on the participants’ substantive contribution to the study design, data analysis, and interpretation, the writing of the article, its critical revision, and final approval before submission.

